## Abstract

**Background:**

Harmful alcohol use is a leading cause of global disability and death. However, increased detection and brief intervention capacity of more severe alcohol use disorders has not been accompanied by increased availability of treatment services. Incorporating treatment for such disorders into primary care is of paramount importance for improving access and health outcomes. This study aims to estimate the effectiveness of a Brief Motivational Treatment (BMT) applied in primary care for treatment of these disorders.

**Methods:**

A parallel-group, single-blinded, severity-stratified, randomized clinical trial will test the superiority of BMT over enhanced usual care. Eligible participants will be those seeking treatment and who fulfill DSM-V criteria for alcohol use disorder and criteria for harmful alcohol use. With an estimated a loss to follow-up of 20%, a total of 182 participants will be recruited and equally randomized to each treatment group. The intervention group will receive an adaptation of the motivational enhancement therapy, as manualized in Project MATCH. This treatment consists of four 45-min sessions provided by a general psychologist with at least 3 years of primary care experience. The primary outcome is the change from baseline in the drinks per drinking day during the last 90 days, which will be captured using the Timeline Follow Back method. Secondary outcomes will describe the changes in alcohol use pattern, motivational status, and severity of the disorder.

All participants will be analyzed according to the group they were allocated, regardless of the treatment actually received. Mean differences (MD) will be computed for continuous outcomes and relative risks (RR) and RR reductions (RRR) for dichotomous results. Linear models will deliver the subgroup analyses. Missingness is assumed to be associated with the baseline alcohol use pattern and severity, so a multiple imputation method will be used to handle missing data.

**Discussion:**

This trial aims to test the superiority of BMT over enhanced usual care with a reasonable superiority margin, over which the BMT could be further considered for incorporation into PC in Chile. Its pragmatic approach ultimately aims to inform policymakers about the benefit of including a brief psychosocial treatment into PC.

**Trial registration:**

ClinicalTrials.gov NCT04345302. Registered on 28 April 2020

## Administrative information

Note: the numbers in curly brackets in this protocol refer to SPIRIT checklist item numbers. The order of the items has been modified to group similar items (see http://www.equator-network.org/reporting-guidelines/spirit-2013-statement-defining-standard-protocol-items-for-clinical-trials/).

## Introduction

### Background and rationale {6a}

Alcohol consumption continues to have a massive negative impact on health. During 2016, the harmful use of alcohol accounted for 5.3% of all deaths and 5.1% of all disability-adjusted life years (DALYs) worldwide, representing a major preventable risk factor for disability and death [1]. Alcohol consumption is associated with digestive diseases, cancer, diabetes mellitus, epilepsy, and cardiovascular diseases, among other health problems. Among the 230 diseases and health problems to which alcohol is related, alcohol use disorders (AUDs) account for 14% of all alcohol-attributable DALYs, preceded only by injuries and digestive diseases [1]. Despite the existence of effective treatment options [2–4], there remains a significant treatment gap between the number of individuals affected by AUDs and those who receive treatment. This is probably the most substantial gap among all mental health disorders [5]. In Chile, less than 5% of people with AUDs received an appropriate intervention during 2014 [6].

The programs for screening, brief intervention, and referral to treatment (SBIRT) attempt to bridge this gap and have resulted in increased detection and provision of brief interventions for risky alcohol usage [7]. However, brief interventions are insufficient for more severe cases (i.e., alcohol dependence) [8]. In Chile, only 11% of people with alcohol dependence received treatment 6 months after the referral from the SBIRT program. A sensible approach to tackle this issue would be to advance the incorporation of services for AUDs in primary care (PC). This strategy could remove several access barriers and make use of the client’s motivational momentum. Additionally, a treatment for alcohol dependence within PC would provide care in a less stigmatizing way. Moreover, such a treatment could contribute to healthcare integration since alcohol use is intimately associated with relevant health outcomes [9].

Evidence of effective options to treat alcohol dependence in PC is still scarce but starting to grow. Finn et al. [10] studied a structured treatment in PC (i.e., the 15-method) in comparison to specialized treatment in secondary care. A 15-min intervention delivered by physicians in primary care behaved similarly to specialist treatment for moderate severity alcohol use disorder, even when clients in PC attended an average of 2.9 visits in contrast to clients in specialist care attending an average of 4.7 sessions. Brown et al. [11] reported another approach to treatment in PC consisting of a telephone and mail adaptation for a psychosocial intervention. They showed mild effects on male participants; however, we know little about the severity of the alcohol use problem, other than half of the participants met diagnostic criteria for dependence and the other half met the criteria for abuse. Finally, Nadkarni et al. [12] studied a four-session treatment for men with harmful alcohol use. In this study, lay counselors delivered the intervention, showing remission of harmful alcohol use in 36% of the participants.

All of these interventions show significant benefits from well-designed treatments that suit the clients’ needs and are coherent with the functioning of PC. Notably, a brief therapy in PC could be the natural continuation of SBIRT programs and provide high quality of care for a variety of clients. The motivational enhancement therapy (MET) [13] is of particular interest to PC because it is short (i.e., four sessions), its efficacy is supported by robust evidence [13, 14], and it is based on the motivational interview (MI) [15], which is a prominent counseling style in PC. In fact, several of MET’s techniques, like personalized feedback and person-centered counseling style, are present in the PC treatment modalities mentioned above.

Even though the effectiveness of MET has been established in well-designed clinical trials, their results cannot be directly extrapolated to PC. Mainly, the larger clinical trials on MET effectiveness (i.e., project MATCH [13] and the United Kingdom Alcohol Treatment Trial [UKATT] [14]) compare it with other active treatments, where specialized counselors provide MET and the active comparator. On these trials, MET showed an effectiveness similar to the other more extensive treatments. However, we do not know if this effectiveness will remain when applied by a general psychologist. In fact, the provider’s professional credentials modify the effect of motivational treatments, with a higher qualification associated with better outcomes [16]. On the other hand, clients with AUDs have access to a variety of unspecialized services in PC; it could be the case in this setting that usual care is adequate for a large number of clients with a mild form of dependence. For instance, a client could have a consultation with a psychologist, access several social services through a social worker, have an appointment with a physician and get a prescription for psychoactive drugs and disulfiram, or be referred to secondary care. In other words, as MET has not been compared with usual care in PC, and as some clients recover from AUDs spontaneously in the community, we cannot anticipate the net effect of MET in this setting. Altogether, the therapy cannot be introduced to Chilean PC without adaptation and local evidence that confirms the effect.

This trial aims to study the effectiveness of a Brief Motivational Treatment (BMT), which is an adaptation of MET’s procedures to Chilean PC, compared to enhanced usual care (EUC).

### Objectives {7}

This exploratory trial aims to estimate the effectiveness of a BMT for AUD provided in PC. The underlying question is whether Chilean PC should incorporate this treatment among its regular programs based on its effectiveness.

To answer this question, we will undertake a randomized comparison between the manualized BMT and EUC. Our main hypothesis is a superiority one:
Participants under BMT will perform better than EUC in the reduction of alcohol consumption.

Also, there are ancillary questions that deserve special attention. The following hypotheses will help with the explanation of the results:
◦ Active BMT components (i.e., the working alliance and fidelity to the MI strategies) mediate the effect.◦ Participant’s AUD severity mediates the effect.◦ Participants under BMT will receive a higher amount of additional care (physician consultations, social worker consultations, participation in alcoholic anonymous, and others).

### Trial design {8}

The study is a parallel-group, single-blinded, randomized clinical trial to test the superiority of BMT over EUC. The allocation ratio is 1:1. The study is also pragmatic: the participants should be representative of PC clients and the study therapists will have a competency profile similar to a regular psychologist in PC [17].

## Methods: participants, interventions, and outcomes

### Study setting {9}

The trial will take place in PC centers in Santiago, Chile.

### Eligibility criteria {10}

#### Participants

The protocol captures typical PC clients to maximize external validity. Hence, participants will be recruited from the SBIRT program currently conducted in PC centers, as well as from physician referrals. Our inclusion criteria follow previous robust clinical trials to enhance comparability (the project MATCH [13] and the UKATT study [14]).

Any client with an Alcohol Use Disorders Identification Test (AUDIT) > 15 will be considered for eligibility. We will include clients who fulfill criteria for alcohol use disorder according to the Diagnostic and Statistical Manual of Mental Disorders V [18] (DSM-V) and criteria for harmful alcohol use during the last month, i.e., five or more heavy drinking occasions in the last month (5 or more drinks in men, 4 or more in women), or an average use of 14 or more drinks a week in men, and 7 or more in women. Also, alcohol use should be the main problem motivating participants to seek treatment. In case of doubts about the eligibility of a potential participant, the criterion to follow is whether this individual would be offered treatment in PC under normal conditions.

Additionally, a clinician will verify the need to refer the participant to a detoxification service before enrolment into the trial, as well as referrals to address any pressing issue (i.e., homelessness, unstable medical pathology, developing legal situation, and so forth).

The participation of a significant other that can help the client through the treatment will be encouraged from the beginning.

#### Exclusion criteria

*Clients under 20 years old*: In Chile, younger clients attend specific providers under a specific administrative regimen (the Explicit Health Guarantees system). Therefore, regulatory restrictions preclude the recruitment of participants under age 20.*Clients in whom alcohol use is not the main problem*: Following the methodology of the UKATT study [14], clients with a problematic consumption of other substances (e.g., marijuana, cocaine) may participate in the trial, provided that alcohol is currently their primary source of problems. Given that the UKATT study demonstrated effectiveness in people with more than one substance use disorder, we will follow that approach to include clients as they exist in the real world.*Clients who leave the area or are unable for follow-up contact*: Participants who will leave the area before completing the 6 months of follow-up or are unable to provide two alternative contacts.*Clients with severe mental comorbidity*: Clients with psychotic disorders, schizophrenia, active suicidal ideation, who currently represent a risk of aggression towards themselves or towards third parties, impulse control disorders, or who have any other severe mental disorder. In this regard, we are following a restrictive exclusion criterion, similar to that of the MATCH project [13]. Additionally, these clients are not treated in PC.*Clients with severe cognitive impairment, illiteracy, or unable to follow treatment in Spanish*.*Clients who are concurrently receiving or planning to receive other psychosocial treatment for AUD other than EUC*, i.e., formal professional treatment outside of PC. Participation in community services and Alcoholics Anonymous is permissible.*Clients who have previously participated in the study* or whose family members are or have been participants.

### Who will take informed consent? {26a}

A certified clinician in the role of research assistant (RA) will take informed consent after confirming participant eligibility. The informed consent will be taken in person, at each clinical site.

### Additional consent provisions for collection and use of participant data and biological specimens {26b}

Participants will be asked for consent to use their anonymized data in scientific publications. No biological specimens will be collected in this trial.

## Interventions

### Explanation for the choice of comparators {6b}

To study the effect of the BMT in PC, we will compare it with usual care as it occurs in Chilean PC. This comparator is relevant since it acknowledges the pragmatic goal of this trial: whether Chilean PC should incorporate this treatment among its regular programs based on its effectiveness.

Although this comparator is appropriate for the research question, its usage raises some problems. The main issue we foresee is a high variability of the services that constitute usual care between different clients and across different PC centers. The services could range from a delay in treatment due to a lengthy waiting list, to multiple timely interventions provided by an organized psychosocial team. In an extreme scenario, if this heterogeneity is too high, it could complicate the statistical analysis.

However, in the real-world scenario where the study will take place, we think it is reasonable to compare BMT against EUC. Based on local data, we assume that over 80% of AUD cases will be waiting for a consultation in the specialized services and, in the meantime, receiving a low level of non-specific services in PC. Thus, these cases compose a homogeneous cohort where we expect the typical evolution of AUD within PC. It is still possible that a proportion of these clients will receive some treatment modality (not BMT) or present spontaneous remission, so we are taking this fact into account for sample size calculation.

### Intervention description {11a}

#### BMT

Participants in the intervention group will receive the BMT, which is a PC adaptation of the MET as manualized in the Project MATCH [19]. This treatment consists of four 45-min sessions, provided by a psychologist at weeks 1, 2, 6, and 12. The first three sessions, occurring during the first 6 weeks, are more active regarding the behavioral change, while the last session functions as closure and review of the process. If a participant asks for more support, they will be able to attend up to two extra sessions before the last one.

The main adaptations to the original Project MET manual are:
The translation into Chilean Spanish.An update of MI concepts used throughout the manual using the last edition of the MI reference book.The addition of companion training material that includes a demonstrative video and practical exercises on the MI strategies.A personalized feedback procedure based on the evaluation used in the trial and the local epidemiological situation.The addition of information on additional resources available in the PC center and the community to be included in the “menu of options.”The addition of a module regarding the coordination of health services in the Chilean PC context. This supplementary material is meant to facilitate the participants’ access to services complementary to BMT within the PC center (i.e., social services, medical services, among others).

#### Selection and supervision of the providers

We will recruit general psychologists or other psychosocial professionals with at least 3 years of experience in PC. They will receive training in BMT and then will demonstrate proficiency in a simulated client session (or will provide a taped interview showing a proficient application of BMT).

During recruitment, therapy sessions will be recorded, and 10% of them will be reviewed using an MI proficiency scale. Then, a feedback report on the fidelity to MI will be issued and discussed with each therapist. The instrument to be used will be chosen during the pilot among the available validated tools [20].

#### Enhancement of usual care

All participants will receive an educational brochure on alcohol use disorder, with self-help materials and guides on how to get additional support.

The physicians within the PC center will also receive information on how to diagnose AUD, prescription guides for the medications that are available for treating these disorders in the PC center (mainly disulfiram and any other if available), and directions on when and where to refer clients for treatment.

### Criteria for discontinuing or modifying allocated interventions {11b}

As the BMT will be added to EUC, all participants will be receiving the current standard of care in Chile. Also, psychosocial treatments based on MI are not expected to induce severe adverse events.

### Strategies to improve adherence to interventions {11c}

Before each session, the participants will receive a confirmation call. They will additionally receive public transportation vouchers for their attendance to assessments.

### Relevant concomitant care permitted or prohibited during the trial {11d}

During the trial, participants will continue to receive regular medical and social care at their health center. These services may include prescriptions for mental health issues and alcohol (disulfiram, anti-craving, anti-depressants, and other medications), social assistance, and the full spectrum of primary health care. Nevertheless, they will not receive other psychosocial interventions for AUD in the health center.

Additionally, participants are asked not to initiate other formal psychosocial treatment for alcohol use disorder until trial termination. This restriction does not include non-professional community services, such as attendance to Alcoholics Anonymous or other informal support.

The study record will keep track of the days when a participant receives additional treatment (if any). Even though it is prohibited, a participant that eventually receives additional formal psychosocial treatment for AUD will continue to receive the allocated treatment and will complete follow-up, and their data will be included to be analyzed according to the original allocation group.

### Provisions for post-trial care {30}

Once the trial has finished, the participants will continue their usual health care at their PC centers. There will not be special post-trial care.

### Outcomes {12}

#### Primary outcome

The primary outcome is the change from baseline in the drinks per drinking day (DDD) during the last 90 days (i.e., the previous 12 weeks), measured at 6 months follow-up. The DDD will be aggregated using means.

The DDD constitutes a relevant outcome because the frequency and quantity in which alcohol is consumed mediate the occurrence of behavioral disorders and health deterioration in clients with AUD. Even though a more comprehensive result, such as clinical recovery or improved quality of life, would be of more clinical significance, these outcomes exceed a short-term, exploratory trial. We have chosen DDD because it has shown to be sensitive to treatment and because it allows comparability with influential clinical trials [21].

#### Secondary outcomes

The number of participants with a low-risk alcohol use pattern estimated by the number of days of consumption, of abstinence, and intoxication during the last 90 days, aggregated using the proportion of participants per group, at 6 months follow-up. Additionally, the most extended period of abstinence since enrolment will be estimated at 6 months follow-up. The number of abstinence days of each participant will be aggregated using means.The change from baseline in the negative secondary consequences of alcohol consumption will be measured using the DrInC-2R questionnaire [22] measured at 6 months follow-up and aggregated using means.The change from baseline in the severity of the AUD using the Substance Dependence Severity Scale (SDSS) at 6 months follow-up [23]. Means will be used to aggregate participants’ DAYS, SEV, and WORST SEV scores for alcohol. The severity of AUD is a critical outcome in two ways: first, we hypothesize that the severity should decrease with treatment; second, severity is expected to predict treatment effect, so it could help identify a specific range of severity in which BMT is more effective.The change from baseline in the motivational stage measured with the SOCRATES scale [22] at 6 months follow-up. The proportion of participants that improve their motivational stage will be used to aggregate the measurement in each group. This scale was designed to classify clients in one of the stages of change according to Prochaska and DiClemente [24] and is expected to mediate client recovery and predict treatment effect.

#### Other instruments

The therapeutic alliance will be measured after each treatment session (four times during the trial) using the Working Alliance Inventory short form in its client and therapist versions (WAI-C and WAI-T) [25].

Finally, we will collect baseline demographic variables (age, sex, years of education, employment status, and marital status).

### Participant timeline {13}

### Sample size {14}

Given that there is a spontaneous reduction of alcohol consumption in control groups of 14% [26], and that the reduction attributed to psychosocial treatments in the literature is around 40% [27], we set a superiority margin δ of 26% reduction in alcohol consumption. The following two hypotheses correspond to the superiority test:
H_0_: DDD_EUC_ − DDD_BMT_ = < δ;H_a_: DDD_EUC_ − DDD_BMT_ > δ.

We used local data and the results of project MATCH as references for sample size calculation. Project MATCH [13] recruited participants with AUD in the outpatient setting and observed a standard deviation (SD) of 6.29 drinks, which is similar to reports in Chilean PC [28]. On admission, participants in the MATCH study consumed 11.5 DDD, which should be similar in our population. We expect a decrease of 14% in the EUC group [26], that is, to 9.89 DDD, and a reduction to 40% in the intervention group [27, 29], that is, a decrease to 6.9 DDD.

The sample size was obtained using the formula for means comparison in superiority studies of parallel groups, according to the methodology described by Chow [30]. The computation was made using the R statistical software [31] with the package provided by the same author [30, 32]. We obtained a sample size of *n*_1_ = *n*_2_ = 76 using the following parameters: *α* = 0.05; *β* = 0.2 : *σ* = 6.29; *δ* = 2.99; *κ* = 1 (where *α* is the type 1 error, [1- *β*] the power, *σ* the standard deviation, *δ* the expected difference between both groups, and *κ* the allocation ratio between both groups).

Considering an expected loss to follow-up of 20%, we will have to recruit 91 participants for each group, which is 182 participants in total.

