## Discussion

The present study will provide initial evidence on the effect of a brief psychosocial treatment for AUD in PC, which is essential in the context of the improved response capacity to harmful alcohol use through the SBIRT programs. The evidence on the effectiveness of such therapies in PC is still scarce, and this trial attempts to provide valuable information on the topic.

Based on previous reports [3, 4, 13], we hypothesized that the BMT would induce at least a 26% reduction of alcohol consumption compared to EUC. We think this is a reasonable superiority margin, over which the BMT could be further considered for incorporation into PC in Chile. The hypothesis will be tested by the analysis of the primary outcome, i.e., the change in the pattern of alcohol use 6 months after recruitment. We are aware that a binary response outcome would have been of more clinical significance; however, this test would have required a larger sample size, so it did not seem appropriate for an exploratory trial.

Some important modifying and predictive variables have been included to explain the results. The severity of the AUD is of cardinal importance since we do not expect BMT to be equally effective in all the spectrum of the disorder. Even though severity did not mediate MET effectiveness in the MATCH project [38], we have to bear in mind that the MATCH study occurred in specialized care settings and not in PC. In addition, PC is supposed to provide care for prevalent disorders in their mild to moderate presentations, so the question about the severity is of high relevance. Other essential modifiers are the fidelity to the intervention and the therapeutic alliance since both have shown to predict the effect of psychosocial interventions [39].

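### The superiority margin equals the expected effect (2.99 drinks), so the hypothesis test as written has power equal to α, not 80%

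*Protocol article*

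**What the plan says.** Sample size {14} takes a 14% spontaneous reduction in controls and a reduction of about 40% under psychosocial treatment, and from these states "we set a superiority margin δ of 26% reduction in alcohol consumption". The null is written "DDD_EUC_ − DDD_BMT_ = < δ" and the alternative "DDD_EUC_ − DDD_BMT_ > δ".

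The next paragraph gives the planning values: "On admission, participants in the MATCH study consumed 11.5 DDD"; "We expect a decrease of 14% in the EUC group [26], that is, to 9.89 DDD"; and 6.9 drinks per drinking day (DDD) in the BMT arm. The parameter list gives α = 0.05, β = 0.2, σ = 6.29 and δ = 2.99, and there δ is defined as "the expected difference between both groups". The result is 76 per arm, raised to 91 per arm for 20% attrition.

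The main Discussion repeats the claim: "we hypothesized that the BMT would induce at least a 26% reduction of alcohol consumption compared to EUC". It calls this 26% a superiority margin and says the primary outcome analysis will test the hypothesis. The Discussion part of the Abstract describes a trial "with a reasonable superiority margin, over which the BMT could be further considered for incorporation into PC in Chile".

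Two other sections carry no margin. Objectives {7} states the main hypothesis simply as BMT doing better than EUC. Statistical methods {20a} and Table 1 plan a t test with a mean difference and 95% confidence interval.

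**The concern.** One symbol and one value serve both as the boundary of the null hypothesis and as the effect the trial expects. These must differ, because the power of a margin test comes from the distance between them, and here that distance is zero.

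There are two ways to go wrong. If the hypotheses are followed as written, a trial in which BMT works exactly as planned fails its primary hypothesis at least 95% of the time. If an ordinary t test against zero is run instead, a significant result may be presented as showing a benefit beyond 26%, which that test does not show. The second risk matters because the protocol ties possible adoption in Chilean primary care to exceeding this margin.

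The percentage is also labelled inconsistently. In Sample size {14} it is a share of baseline consumption, while the main Discussion describes it as a reduction compared with EUC. These are different quantities.

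**Working it through.** **Inputs**, all from Sample size {14}: baseline 11.5 DDD; reductions 14% (EUC) and 40% (BMT); σ = 6.29; α = 0.05 with sidedness not stated; β = 0.2; 1:1 allocation; 76 per arm evaluable, 91 per arm recruited.

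**1. Margin and expected effect.**
- EUC mean: 11.5 × 0.86 = 9.89. BMT mean: 11.5 × 0.60 = 6.90.
- Expected difference: 9.89 − 6.90 = 2.99.
- Margin: 26% of baseline = 0.26 × 11.5 = 2.99.
- The two are identical, since 26% is 40% − 14%.

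**2. The protocol's own sample size.** Per arm, n = 2 × [σ(z_α + z_β) / (expected difference − null value)]².
- Null value 0, two-sided 0.05, 80% power: 69.5, so 70 (71 with the t distribution).
- Null value 0, one-sided 0.05, 80% power: 54.7, so 55 (56 with the t distribution).
- Null value 0, one-sided 0.05, 90% power: 75.8, so 76.
- Null value 2.99, as the hypotheses state: the denominator is 2.99 − 2.99 = 0, and no finite n exists.

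The printed 76 does not follow from β = 0.2; among these variants it appears only with the 90% power quantile. In every variant that gives a finite n, the full 2.99 is the distance from the null, so the null value is zero.

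**3. Power of the test as written.** Power = Φ[(true difference − margin) / SE − z(1−α)], with SE = 6.29 × √(2/76) = 1.020.
- At true difference = margin = 2.99 the first term is 0, so power = Φ(−z(1−α)) = α: 5% at one-sided 0.05, 2.5% at one-sided 0.025. Neither n nor σ affects this.
- A simulation with 76 per arm (means 9.89 and 6.90, SD 6.29, one-sided 0.05, margin 2.99) rejected in 4.96% of trials.

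**4. True difference needed for 80% power against the 2.99 margin at 76 per arm.**
- One-sided 0.05: 2.99 + (1.645 + 0.842) × 1.020 = 5.53.
- One-sided 0.025: 2.99 + (1.960 + 0.842) × 1.020 = 5.85.
- The t distribution gives 5.54 and 5.87.
- Implied BMT means: 9.89 − 5.53 = 4.36 and 9.89 − 5.85 = 4.04, falls of 62% and 65% from 11.5, against the 40% assumed.

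**5. Power of an ordinary test against zero, true difference 2.99, two-sided 0.05.**
- 76 per arm: 83.4%.
- 73 per arm (91 × 0.8 = 72.8 after the stated attrition): 81.9%.
- An observed difference of about 1.96 × 1.020 = 2.0 drinks would already be significant at 76 per arm, well short of 2.99.

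**6. The percentage label.**
- 2.99 / 9.89 = 30.2% relative to EUC.
- 26% relative to EUC is 0.26 × 9.89 = 2.57 drinks.
- With 2.57 as the margin and 2.99 as the true difference, power at 76 per arm is 10.8% (one-sided 0.05) or 6.1% (one-sided 0.025). Reaching 80% would take 2,792 or 3,545 per arm.
- With 2.57 as the true difference and a zero null, two-sided power is about 71% at 76 per arm and 69% at 73.

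**The case against.** The strongest reply is that nobody intends a margin test. Objectives {7} asks only whether BMT is better than EUC, Table 1 plans an ordinary t test, and the parameter list itself defines δ as the expected difference. On that reading the margin is a mislabelled planning effect, the 5% power never arises, and the planned recruitment gives about 82–83% two-sided power. The trial calls itself exploratory, and the planned 95% confidence interval would show readers whether 2.99 is excluded.

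Much of this stands. The likeliest explanation is that the margin was confused with the expected difference, and under a zero null the trial is adequately sized for 2.99 drinks. The 5% figure describes what happens if the written hypotheses are followed, not a forecast of what the team will do. Nor does the protocol say that a significant t test will be reported as exceeding 26%; it creates that risk. The main Discussion's 26% compared with EUC may be loose wording for 26 points more reduction than EUC, so the 2.57-drink figures measure an ambiguity, not the protocol's plan.

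The error itself remains. The null and alternative are printed with δ in them, and the main Discussion says the primary analysis will test the 26% hypothesis and treats the margin as the threshold for considering adoption. That conflicts with Objectives {7} and Table 1, and no analysis can satisfy both.

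**Conclusion.** The concern holds. As written, the primary hypothesis test has power equal to its type I error at the planned effect: 5% or 2.5% depending on sidedness, against the 80% claimed. This follows from the margin equalling the assumed difference and does not depend on σ, on n, or on whether 76 can be reproduced. The protocol states two incompatible primary hypotheses, and its sample size and t test match only the zero-null one. Under that null, two-sided power is about 82–83% at 73–76 per arm, assuming a true difference of 2.99 and SD 6.29. The defect is therefore in the stated hypotheses and the claim built on them, not in the number recruited. It must be corrected before analysis, because it determines what a positive result means.

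**What to change.** Restate the hypotheses in Sample size {14} with a zero null: H0: DDD_EUC − DDD_BMT = 0 against a two-sided alternative at α = 0.05, which matches the 95% confidence interval already planned. Call 2.99 drinks the difference assumed for sample size, and describe it as 26 percentage points of baseline, or 30% relative to EUC. Remove the superiority-margin wording from Sample size {14}, the main Discussion and the Abstract. State that success means excluding zero, and that the confidence interval will be read against 2.99 to judge clinical relevance, which keeps the threshold in view for policymakers.

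The cost is a wording amendment, submitted to the ethics committee as the protocol's section on amendments {25} requires for changes to sample size calculations or statistical analysis. No extra participants are needed. The price is a weaker claim: better than EUC, not better by at least 26%.

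If the sponsor wants to keep a true margin, it must be justified, set below the assumed effect, and n recomputed. As illustrations (these margins are not in the protocol), with a true difference of 2.99 and 80% power, a margin of 1 drink needs 124 evaluable per arm (one-sided 0.05) or 157 (one-sided 0.025). A margin of 1.5 drinks needs 221 or 280.
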